## **2.5 Monitoring**

### **2.5.1 Data monitoring**

#### ***Data monitoring committee***

Since this is a short study, we do not need data monitoring committee for this pilot study. However, independent personnel from Clinical Epidemiology and Evidence-Based Medicine (CEEEM) Unit, [name] Hospital (CMH) – Faculty of Medicine Universitas Indonesia (FMUI), who is not involved in this study, will assess the process and the quality of patient recruitment, data entry, and a compilation of research data in central database. Her feedback will be important to improve the implementation of our main study.

#### ***Interim analysis***

Due to the small number of recruited patients to the trial and the duration of the trial will be lesser than one year, we will not perform an interim analysis.

### **2.5.2 Harms**

An adverse event is defined as any untoward medical occurrence in a patient or clinical investigation subject administered a pharmaceutical product and which does not necessarily have to have a causal relationship with trial drug; whereas adverse effects or adverse drug reaction, is defined as all noxious and unintended responses to a trial drug related to any dose.

At the Visit-2 (Day-3), the appointed nurse is the first person who will identify any adverse effects (AEs). These will be identified by history taking (e.g. interview) and the symptom diary. The parents will provide information in the symptom diary regarding the adverse effects and whether they seek any treatment or medical assistance to manage AEs. The nurse then will report the adverse effects to the physicians along with the information of the intervention group which the child was allocated to. This information will be provided after the physician assess and record the primary outcome (i.e. ear pain three days after the randomization) on the 'Outcome form'. This is important to keep the concealment.

Adverse events and adverse drug reaction will be collected after they sign the written consents and being enrolled in the trial. All adverse events occurring after the enrolment into the study, during the additional treatment or hospitalization due to adverse events and/or ADR will be

recorded. A subject who experiences a serious adverse event (SAE), defined as any untoward medical occurrence at any dose that may result in-patient and/or prolonged hospitalization, persistent or significant disability, medically important events, life threatening events, and death, will receive sufficient treatment and will be recorded and reported to the Research Committee Ethics FMUI – CMH and the Bond University’s Human Research Ethics Committee (BUHREC). We will be responsible for any additional examinations and/or treatment that are required to manage AEs.

We will not report SAE occurring after the trial discontinuation, unless there is a temporal relationship between trial drugs or other protocol procedure to the events, as well as whether the event is unexpected or unexplained given the subject’s clinical course, previous medical conditions, and concomitant medications. All the SAE will be recorded in SAE form.

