### **2.2.3.4 Concomitant care and interventions**

Physicians may give symptomatic medicine (i.e. ibuprofen, acetaminophen, decongestant, mucolytic) according to their usual practice and these will be recorded in the CRFs and symptom diary. Parents will record the use of these medicine in the symptom diary. The decision on concomitant medication will be made without knowledge of allocation to the prednisolone or control group.

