## Participant enrolment

In the main study, we will stratify eligible children by the clinical specialty (primary care or secondary/tertiary care) and severity of AOM (mild or severe). However, we only include ear-nose-throat-specialists (ENTs) who work at tertiary care in this pilot study. Therefore, we will stratify the children based on their AOM severity and then will randomly allocate these eligible children to receive either a single dose prednisolone for five days or without, as an addition to expectant

observation in the mild AOM group or as an addition to antibiotics according to physicians' preferences (e.g. antibiotic type, dose, duration) in the severe AOM group (see Figure 1).

[figure not shown]

**Figure 1.** Flow chart of the stratification and randomization of the study

Participating physicians will assess the eligibility of children who come to the hospital based on their symptoms and clinical features of AOM. The eligible children will then be stratified based on the severity of AOM to either mild or severe AOM group. This process will be assisted using an eligibility and randomisation form. The participating clinicians will then obtain a clinical history and perform a baseline examination, including general, otoscopic, and tympanometry examination. The results of these procedures will be recorded at the baseline history form and outcomes form. The tympanometry examination will be conducted by an audiologist or a tympanometry technician. The physician will assess and analyse the tympanometry findings and record the results in the outcome form. After these procedures, the children will be sent to the appointed nurse who will perform the randomisation and dispense the prescription for a study medication (prednisolone) if the patient is assigned to the intervention group.

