### ***Allocation concealment mechanism and implementation***

The information of the eligibility and stratification which is provided by the participating physicians will help the appointed nurses to obtain the information from the randomisation website, whether the children will be allocated to the prednisolone or control group, identified by the 2-digit patient ID numbers. During the consultation, the physician will prescribe study medication for every subject with the dose based on the patient age and insert the prescription in the CRF folder. The nurse who performs the randomisation will give the prescription to the subjects who are allocated to the intervention group (prednisolone group). The subject then will give the prescription to the pharmacy, where the pharmacist will prepare the prednisolone by crushing the tablets, mixing them with sweeteners, packing the prednisolone mixed powder in a daily individual paper-pack for five days, and dispense these to the subjects along with instructions for preparation. The pharmacist will record the dispensing on the form provided by the study for this purpose.

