### **2.3.2 Blinding (masking)**

In this study, the appointed nurses and the children and their parents will know the allocation of the intervention. We will ensure that the participating physicians and the audiologists/tympanometry technicians will be blinded to the intervention allocation during the study.

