### ***Emergency unblinding***

The unblinding process should be done if there are serious adverse events and limited only to that particular participating physician.

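### Section 2.5.2 tells the outcome-assessing physician the child's arm with any adverse effect reported at Day 3, contradicting the protocol's own blinding rules

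*Protocol*

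**What the plan says.** The pilot has no placebo. Parents and the randomising nurse know the allocation. Sections 1.1.3, 2.1, 2.3.1 and 2.3.2 name two groups who should not: the participating physicians, and the audiologists or tympanometry technicians. Section 2.3.2 says that these groups "will be blinded to the intervention allocation during the study". Its emergency rule reads: "The unblinding process should be done if there are serious adverse events and limited only to that particular participating physician". Section 2.2.3.4 adds: "The decision on concomitant medication will be made without knowledge of allocation to the prednisolone or control group".

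Section 2.5.2 sets out a different flow of information. At Day 3 the nurse asks about adverse effects, checks the diary, and is to "report the adverse effects to the physicians along with the information of the intervention group which the child was allocated to". The one safeguard is the order of events: "This information will be provided after the physician assess and record the primary outcome", meaning ear pain three days after randomisation. The section says that this order preserves concealment.

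On the physician's part in tympanometry, the enrolment text in Section 2.2.5 says: "The physician will assess and analyse the tympanometry findings and record the results in the outcome form". The examination itself is done by an audiologist or technician.

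**The concern.** Assessor blinding is what makes this open-label pilot single-blind. A physician who learns the arm at Day 3 still has assessments ahead. Table 1 schedules otoscopy at Days 7, 30 and 90, complications at Day 7, and recurrence at Days 30 and 90. The physician may also decide on further treatment once the 48-hour observation of mild cases ends.

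The disclosure is also unlikely to fall evenly on the two arms. Section 2.5.2 defines an adverse effect as a response to a trial drug, and controls receive neither drug nor placebo. Any effect of knowing the arm on later judgements would therefore fall mainly on prednisolone children and could bias the comparison.

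In addition, staff cannot follow Sections 2.3.2 and 2.5.2 together. In a pilot meant to test the procedures of a larger trial, that is a defect in its own right.

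**Working it through.** The plan gives no figure on this point to reproduce, so the main check sets the passages side by side.

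**1. Trigger for disclosure.** Section 2.3.2 ties unblinding to serious adverse events. Section 2.5.2 ties it to any adverse effect. The two rules differ for every non-serious effect.

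**2. Duration of blinding.** Section 2.3.2 covers the whole study. Under Section 2.5.2, blinding ends at Day 3 for a child with a reported effect.

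**3. Co-treatment.** Section 2.2.3.4 holds for prescribing at baseline, which precedes randomisation. It fails for any decision made after the arm has been disclosed.

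**4. What the ordering protects.** It protects the Day-3 ear-pain record. It does not expressly protect Day-3 tympanometry. It protects nothing at Days 7, 30 or 90, which are three of the four follow-up time points for middle ear effusion in Section 2.2.4.2.

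**5. Who is unblinded.** Only the physician. Section 2.5.2 does not pass the arm to the audiologist or technician. The sub-study's primary outcome is static acoustic admittance, an instrument value.

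**6. Visit label.** Section 2.5.2 attaches Day 3 to visit 2. Sections 2.2.3.3, 2.2.4.2 and 2.2.5 make Day 3 visit 1 and Day 7 visit 2. Because Section 2.5.2 refers to pain three days after randomisation, Day 3 is evidently meant and the visit number is the slip.

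**7. Scale.** Assume 30 children per arm (60 randomised 1:1). Expected number disclosed = 30 × rate, using the steroid-arm rates in Section 1.1.2 (Potential harms):

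| Cited figure | Rate | 30 × rate |
|---|---|---|
| Aggressive behaviour, lower dose, 0/43 | 0% | 0 |
| Vomiting requiring discontinuation, 1/343 | 0.3% | 0.1 |
| Anxiety, lower dose, 2/43 | 4.7% | 1.4 |
| Vomiting, 3/41 | 7.3% | 2.2 |
| Vomiting, 10/66 | 15.2% | 4.5 |
| Anxiety or aggressive behaviour, higher dose, 9/43 each | 20.9% | 6.3 |

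This gives roughly 0 to 6 prednisolone children. The only placebo rate quoted beside these is 1/40 for vomiting, which gives 30 × 0.025 = 0.75 control children against 2.2 on prednisolone. On the literal definition of adverse effect, every disclosure would be in the prednisolone arm.

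These rates come from wheeze and asthma trials with other doses and durations. They are not Day-3 rates in otitis media. Each covers a single effect, so the proportion with any effect could be higher. They show order of magnitude only.

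**The case against.** The authors sequenced the disclosure deliberately. It follows the Day-3 ear-pain record, which is the planned primary outcome of the main trial. Clinical outcomes in the pilot are to be reported only narratively, and the main trial is planned as double-blind with placebo. The emergency rule does not say in so many words that serious events are the sole ground for unblinding, so Section 2.5.2 could be read as a second, separate ground. Section 1.1.2 also cites a prednisolone trial in otitis media with no significant difference from placebo in moderate side effects.

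Much of this stands, and it limits the harm. It does not remove the contradiction. A second ground for disclosure still cannot be squared with blinding throughout the study or with blinded co-treatment decisions.

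Four stronger readings are tempting, and the protocol does not support them:

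- *The physician is the only blinded assessor.* Audiologists and technicians are also blinded and remain so.
- *All later tympanometry readings of affected children are made by an unblinded physician.* The examination is done by the audiologist or technician, and the physician's analysing role is stated only for enrolment. Its extension to later visits is plausible because no other reader is named, but it is an inference.
- *Every child is affected.* Only those with a reported adverse effect are.
- *The prescription procedure also reveals the arm.* Section 2.3.1 says "The nurse who performs the randomisation will give the prescription to the subjects who are allocated to the intervention group". It does not say that control prescriptions stay where the physician would later see them. That leak would be inferred from silence.

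**Conclusion.** The concern holds as an internal contradiction with a limited but real risk of bias. Section 2.5.2 unblinds the physician, one of two blinded assessor groups, for any adverse effect reported at Day 3. That conflicts with both rules in Section 2.3.2 and with Section 2.2.3.4.

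For the children concerned, the exposure covers the physician's later otoscopy, any interpretation of tympanograms, complication and recurrence assessments, and co-treatment decisions. The machine-measured admittance is less exposed, and the Day-3 ear-pain record is protected by the stated order.

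The number of children is unknown. Roughly 0 to 6 on prednisolone follows from an assumed 30 per arm and the cited single-effect rates. That disclosures would fall mostly on prednisolone is an inference from the definition of adverse effect and the absence of placebo; the protocol does not say so. The contradiction itself does not depend on the count.

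**What to change.** Reconcile Section 2.5.2 with Sections 2.3.2 and 2.2.3.4:

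- Have the nurse report non-serious adverse effects to the assessing physician without the allocation. Send allocation-linked information to the research team, which already assesses adverse events under Section 2.2.3.2.
- Leave the existing serious-event unblinding in Section 2.3.2 intact.
- Record each unblinding (child, date, arm) and report the numbers by arm.
- Correct the Day-3 label in Section 2.5.2 to visit 1.

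A re-analysis that drops readings made after unblinding is not advised. It would remove children selected by a post-randomisation event related to arm, and so add selection bias.

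The cost is an amended paragraph, a matching check of the two other sections, a short unblinding log, one line in the results and a point in nurse training. No extra visits or measurements are needed.

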### **2.5.3 Auditing**

For the main study, we will establish an audit committee from the CRSU FMUI and CEEBM Unit CMH-FMUI which is independent from the trial investigators and the funding body. However, this will not occur separately from monitoring for the pilot study. This independent committee will conduct monitoring of source paper and electronic documents in the website system, monitor the conduct of trial in multicentre sites, interviewing the investigators and coordinators, and check the storing, distribution, and the use of trial drugs. At the start of the trial, the committee will ensure that the research staff are capable in data entry and in using the website system. Observation and quality assessment of the whole trial will be ensured to be always in accordance with the protocol and International Conference Harmonization – Good Clinical Practice (ICH-GCP) standards.

## **2.6 Ethics and dissemination**

### **2.6.1 Research ethics approval**

This study will be conducted according to the Declaration of Helsinki and ICH-GCP guidelines. We will seek ethics approval from: (1) the Bond University’s Human Research Ethics Committee (BUHREC) Bond University, Queensland, Australia; (2) the Medical Ethics Committee of the Faculty of Medicine Universitas Indonesia – [name] General Hospital, Jakarta, Indonesia; (3) the Directorate-General for Politics and General Government – The Ministry of Internal Affairs Republic Indonesia; (4) the Health Agency for the Province of DKI Jakarta; and (5) local research committee at each participating hospital.

### **2.6.2 Protocol amendments**

Any modifications to the protocol which may impact on the trial process (e.g. the modification of study objectives, study design, study population, sample sizes, the procedures, and significant administrative sectors), potential benefits and harms/safety of the patients will require a formal amendment to the protocol. This amendment will be notified and approved by the funding body and the Ethics committee prior to its implementation. Notification is also applied to the health authorities in accordance with local regulations. Minor modifications that may not impact on the trial process will also be notified and approved by the funding body and will be notified to The Ethics Committee.

### **2.6.3 Consent**

The participating physician will provide patient information sheet and obtain informed consent from the parent(s) or legal guardian of patients, before conducting the recruitment and

randomisation process. In obtaining the consent, the investigators will inform the trial process including known and potential risks from the trial. As children are considered a vulnerable population, those aged younger than 12 years old are considered not competent to give research consent and the parent or their legal guardian will make the decision. The parent can also make decision for children aged 12 years, however there should be assent from children to participate in the research. For parents who are illiterate, we will identify the literacy level before we start the informed consent session and will ensure that the language used in the oral and written information about the trial, including the written informed consent form, should be understandable to the parents and justified to their literacy level. During the process, the participating physician will confirm the participant's understanding of the process of the trial, including the risks and benefits. For particularly crucial topics, the participating physician will ask several questions related to that topic to ensure they are well-informed and understand. Gaining informed consent will be a major topic discussed during training sessions for staff.

The person who delivers the consent (i.e. participating physician, research assistant) also will provide their signatures on the consent form, stating that they have provided information and opportunity for potential participants to understand and raise relevant questions according the trial. We will ensure that the consent process is free of coercion. As the participation into the trial is voluntary, we will emphasise their rights to withdraw from the trial at any time without any consequences, particularly on the quality of their healthcare services.

#### **2.6.4 Confidentiality**

All information related to the trial will be stored securely at the study site and the research office. All participant information will be stored in locked file cabinets in areas with limited access. All data collection, including CRFs, test results, and administrative forms will be kept confidential by only using coded IDs as identifiers and will be stored separately from all forms and records that contain names or other identifiers (e.g. informed consents forms). All databases will be secured with limited access using password-protected access systems. All counselling sessions and general to specific examinations (e.g. ear, nose, throat examination, otoscopic and tympanometry examination) will be conducted in private rooms in the participating physicians' clinics or hospital. All the involved research staffs such as physicians, nurses, and audiologists will be required to sign agreements to preserve the confidentiality of all participants.

The confidentiality of every participant will be maintained and will not be distributed externally without the written permission of the participant, except as necessary for trial monitoring by national regulatory authorities related to the medical and research safety.

## **2.6.6 Access to data**

The Principal Investigator will be given access to the cleaned data sets. She will also have direct access to each sites' data sets and by request. Project data sets will be secured using password. To ensure confidentiality, data dispersed to project team members will be blinded of any identifying participant information.

## **2.6.7 Ancillary and post-trial care**

Short-term corticosteroids are very unlikely to have harm outside those we will be measuring. However, we will be responsible for the adverse effects that occurring from the trial drug during the trial (immediate) and post-trial (ancillary care) related to trial drug. The compensation will include the treatment cost relevant with the trial drug, such as the consultation visit, additional examinations, and treatment (e.g. medicine, hospitalization cost). Due to other potential concurrent treatments within the drug trial, there will be robust review and analysis process to conclude the cause of adverse events. Participating physicians will explain the procedure for the management of adverse effects of trial drug during the process of consent approval before entering the trial. We will also include this information on the patient symptom diary, including the 24-hour emergency call and list of recommended healthcare providers.

## **2.6.8 Dissemination policy**

### **2.6.8.1 Trial results**

Trial results, either statistically significant or non-significant, and other components of the trial (literature review, survey study, pilot study, etc.) will be reported in a journal manuscript after being distributed to all the principal investigators to be reviewed.

### 2.6.8.3 Reproducible research

We will make the full protocol of this study to be publicly available to maintain its transparency and reproducibility. This full protocol will include detailed information regarding the study, particularly on study design and conduct that not are commonly include in the published protocol or information description in clinical trial registry. We will register the protocol into trial registry such as the Indonesia registry web portal (<https://www.ina-registry.org/>) and Australian New Zealand Clinical Trials Registry (<http://www.anzctr.org.au/>). We also will publish the results of this study in relevant medical journal as two separate papers as the following: (1) results of the pilot study and (2) results of the mechanistic sub-study. If necessary, we will include the anonymised participant-level dataset in its appendix or online. Unpublished outcomes will be reported in the full trial report that will be linked to the published study.

